#### Analyses

Repeated-measures ANOVA will be used to compare both the intervention and control group participants on primary and secondary outcome measures, at the 3-month and 9-month assessments. To identify personal characteristics of participants and features of their environment that are associated with better outcomes multiple regression will be used. Significance will be set to *p* < 0.05. Analysis will be on the basis of intention to treat, with a secondary per-protocol analysis.

For the economic evaluation a trial based cost-effectiveness analysis, taking a health system perspective, will compare the two exercise interventions with one another and, separately, with usual care (i.e., our control group). The economic evaluation will estimate the incremental cost-effectiveness of each of the interventions in terms of cost per quality adjusted life year gained. Participant level costs associated with use of health services and medications will be derived from proxy-reported utilisation at each follow-up and costed on the basis of standard published costs (e.g., Australian Refined Diagnosis Related Groups cost weights for hospitalisation and Medicare Benefits Schedule and Pharmaceutical Benefits Scheme [PBS] rates for medical services and prescribed medications respectively). Quality of life will be assessed by the HUI 2 via proxy and converted into health state utilities via the UK scoring system [28].

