### Outcome assessments

All outcomes will be assessed at baseline, 3-months post-baseline and at 9-months post-baseline. Participants and assessors will be un-blinded. The primary outcome measures are aerobic fitness, energy expenditure and physical activity. Secondary outcomes include intervention compliance, participation in domestic activity, objectively assessed physical activity and sedentary time, muscle strength, functional walking capacity, health care utilisation and cost, quality of life, body composition and psychosocial measures.

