### Statistical analyses

#### Sample size

We will power the study based on the primary outcome of aerobic fitness (VO_2_peak; ml•kg•min^-1^). Our MVI-Exercise approach is similar to a previous study that used a 12-week gym-based intervention for people with ID [27]. They reported substantially better post-test aerobic fitness outcomes (assessed by VO_2_peak) for the intervention group relative to controls (large effect size, Cohen’s d = 0.91). Assuming an effect size of d = 0.80 (equivalent to f =0.40), and using a design with three groups and three repeated measures, power calculations with alpha = 0.05, power = 0.95, and a correlation among repeated measures of 0.5 show that this would require a total sample size of 69 (i.e., 23 per group), to analyse between-group differences using repeated measures ANOVA. Our assumptions are conservative so as to avoid under-powering the study. Therefore, we will recruit 30 participants per group for a total sample of 90, which allows for 23% attrition without compromising power.

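### Baseline values of every primary outcome are analysed as one more response instead of a covariate, which gives up about 8 to 11 points of power per arm comparison on the plan's own assumptions

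*Protocol article*

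**What the plan says.** Under Outcome assessments, the protocol article states: "All outcomes will be assessed at baseline, 3-months post-baseline and at 9-months post-baseline". It adds: "The primary outcome measures are aerobic fitness, energy expenditure and physical activity". Every primary outcome therefore has a baseline value.

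The Sample size section works from "using a design with three groups and three repeated measures", with "power calculations with alpha = 0.05, power = 0.95, and a correlation among repeated measures of 0.5", and concludes that "this would require a total sample size of 69 (i.e., 23 per group), to analyse between-group differences using repeated measures ANOVA". Only three assessments exist, so the three repeated measures must include baseline.

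The Analyses section names one method for comparing groups: "Repeated-measures ANOVA will be used to compare both the intervention and control group participants on primary and secondary outcome measures", with the comparison at 3 and 9 months. No section names a baseline covariate or an analysis of covariance (ANCOVA). Multiple regression appears only as a way to find personal and environmental characteristics associated with better outcomes.

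**The concern.** When baseline is a response, a repeated-measures ANOVA offers two tests of treatment. The group-by-time contrast compares changes from baseline. The group main effect averages the arms over all visits, including the one before treatment. Neither makes the best use of the baseline value. A change score subtracts the whole baseline value, although only a fraction (the correlation) predicts follow-up, so it adds noise. The main effect includes a visit at which randomised arms are not expected to differ, which dilutes the effect.

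With 30 per arm planned and 23 per arm after the attrition allowed for, some chance imbalance at baseline is likely. Given an observed imbalance, the change contrast over-corrects for it, and the visit-averaged contrast carries it into the estimate. Covariate adjustment corrects by the estimated slope. At stake are intervals wider than necessary for every arm comparison on all three primary outcomes.

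**Working it through.** **Inputs (Sample size section).** Three arms; three measures; d = 0.80, f = 0.40; alpha 0.05; correlation ρ = 0.5; 23 per arm (69 in total) after attrition, 30 per arm (90) recruited. Variances below are in units of the outcome variance and assume equal correlation between visits.

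**1. The plan's own figure.** For the between-groups effect, λ = f²·N·m / [1 + (m − 1)ρ], with 2 and N − 3 degrees of freedom.
- N = 69: λ = 0.16 × 69 × 3 / 2 = 16.56, power 95.5%.
- N = 66: λ = 15.84, power 94.5%.

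So 69 reproduces, as a test of the group effect averaged over all three measures.

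**2. Variance of each estimator at ρ = 0.5.**

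| Estimator | One visit | Mean of 3 and 9 months |
|---|---|---|
| Follow-up only | 1.00 | (1 + 0.5)/2 = 0.75 |
| Change from baseline | 2(1 − 0.5) = 1.00 | 0.75 + 1 − 2(0.5) = 0.75 |
| Baseline as covariate | 1 − 0.5² = 0.75 | 0.75 − 0.25 = 0.50 |

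The covariate reduces the variance by 25% at one visit and by 33% for the follow-up mean. In general 2(1 − ρ) − (1 − ρ²) = (1 − ρ)², so adjustment never has the larger variance.

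**3. Power for one pairwise comparison.** Noncentral t, two-sided 0.05, noncentrality 0.80/√v × √(n/2), with 2n − 2 degrees of freedom (2n − 3 with the covariate). For n = 23 at one visit the noncentrality is 2.71 with v = 1.00 and 3.13 with v = 0.75.

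| Target | n per arm | Change | Covariate | Gain (points) |
|---|---|---|---|---|
| One visit | 23 | 75.6% | 86.5% | 11 |
| One visit | 30 | 86.1% | 94.0% | 8 |
| Follow-up mean | 23 | 86.5% | 96.3% | 10 |
| Follow-up mean | 30 | 94.0% | 99.1% | 5 |

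Pooling the error over three arms gives 76.2% to 87.0% (n = 23) and 86.5% to 94.3% (n = 30) at one visit. Simulating the covariate model (40,000 replicates), so that the cost of estimating the slope is counted, gives 85.7% and 93.6%. The one-visit gains are then about 10 and 7 points.

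**4. Three-arm test, one arm differing by 0.80 at both follow-ups (4,000 simulated replicates).** Group-by-time power is 82% with 23 per arm, against 97% for ANCOVA of the follow-up mean. With 30 per arm it is 92% against 99.6%.

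**5. If the test is the group main effect.** A difference of 0.80 at both follow-ups and none at baseline averages (0 + 0.80 + 0.80)/3 = 0.53. The mean of three visits has variance (1 + 2 × 0.5)/3 = 0.67. Three-arm power is 48% to 60% with 23 per arm and 60% to 73% with 30. The lower figures are for follow-up means 0, 0.4, 0.8; the upper are for the third arm equal to either extreme.

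**6. Sensitivity to ρ (assumed values), one visit, change against covariate.**

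| ρ | n = 23 | n = 30 |
|---|---|---|
| 0.3 | 61.1% to 79.4% (+18) | 73.1% to 89.1% (+16) |
| 0.6 | 84.3% to 91.2% (+7) | 92.6% to 96.8% (+4) |
| 0.7 | 92.9% to 96.0% (+3) | 97.6% to 98.9% (+1) |
| 0.8 | 98.7% to 99.3% (under 1) | 99.8% to 99.9% (+0.1) |

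**The case against.** The strongest objection is that the article does not spell the model out. The Analyses section speaks of comparison at 3 and 9 months without saying that baseline is a response, and the count of three measures stands only in the sample size paragraph. The article is condensed, and an analysis plan that is not shown could add baseline adjustment. This does not remove the point. The article does name a model and sizes the trial on it, so adjustment would be a departure from what is written. If the ANOVA used follow-up visits only, the variance would be 1.00 against 0.75, the same loss at ρ = 0.5.

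Second, the gain depends on ρ. The 0.5 has no stated source, and the trial is sized on fitness alone, so nothing shows that 0.5 holds for armband energy expenditure or the proxy questionnaire. This stands: on the change-score reading the gain nearly vanishes at ρ = 0.8. Still, 0.5 is the plan's own value. On the follow-up-only reading a higher ρ makes the loss larger: at ρ = 0.7 and 23 per arm it is 75.6% against 96.0%.

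Third, the figure of 8 to 11 points belongs to one pairwise contrast at one visit, not to the main effect that gives 69, and it is about one point high once slope estimation is counted. Both remarks are right. On the main-effect reading the loss is larger.

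Finally, the planned analysis is valid: over repeated randomisation the change contrast is unbiased. That is also right, and it makes this an efficiency point.

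**Conclusion.** The concern holds. As written, the plan uses a less precise estimator than its own data allow. With d = 0.80, ρ = 0.5, two-sided alpha 0.05, one pairwise comparison at one visit and the change-from-baseline reading, it gives up about 8 points of power at 30 per arm and 11 at 23 (about 7 and 10 by simulation). Follow-up visits alone lose as much at that correlation; the visit-averaged main effect loses more. The size rests on the plan's ρ and on equal correlation between visits. The direction does not depend on the value of ρ, apart from the trivial cost of estimating the slope. This should be changed, but it does not invalidate the planned comparison.

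**What to change.** In the Analyses section, replace the repeated-measures ANOVA for the primary and continuous secondary outcomes with a model in which only the 3- and 9-month values are responses. Fit arm, visit and arm-by-visit as factors, and the participant's baseline value of the same outcome, with baseline-by-visit, as a covariate. Report the adjusted arm differences at 3 and at 9 months. A separate ANCOVA at each visit, adjusted for baseline, would also serve.

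The cost is a change of wording and one degree of freedom per visit. No extra data, visits or participants are needed. State how a missing baseline value will be handled, for example by mean imputation; few should arise, since baseline assessment is planned for everyone.

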**Methods/Design:**

A three-arm randomised controlled trial (RCT) will be conducted. Ninety adults with ID aged 18-55 will be randomly assigned to one of three groups: 1) a lifestyle physical activity group (*n* = 30), 2) a structured exercise group (*n* = 30), or 3) a usual care control group (*n* = 30). Participants in both groups will receive a 12-week intervention delivered by exercise specialists in the community with disability service staff, after which intervention will continue for 6 months, delivered by disability service staff only. Primary outcomes are aerobic fitness, 12-hour energy expenditure, and proxy-reported everyday physical activity. Secondary outcomes include objectively assessed physical activity and sedentary behaviour, intervention compliance, functional walking capacity, participation in domestic activities, muscle strength, body composition, psychosocial outcomes, quality of life and health care costs.

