Physical activity is an important national policy issue in Australia [13]. The objective of this project is to improve the physical activity, aerobic fitness, strength and well-being of adults with ID by increasing their everyday physical activity and exercise levels in a manner that is sustainable in the long-term. This will involve comparing two approaches to disability staff support of physical activity by adults with ID: (I) a lifestyle physical activity (light-moderate intensity [LMI] lifestyle) approach and (II) a structured exercise (moderate-vigorous intensity [MVI] exercise) approach. The effectiveness of the two strategies for increasing physical activity and exercise in adults with ID will be evaluated and compared to a usual-care control group. By contrasting two different approaches to increased physical activity we will compare the short-term (3-month) and long-term (9-month) effectiveness and sustainability of both strategies. In addition, the project will evaluate the cost-effectiveness of both strategies.

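### Three primary outcomes of equal status are tested at one flat p < 0.05, which gives about a 10–14% chance of a false positive primary finding if neither intervention works

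*Protocol article*

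**What the plan says.** The Outcome assessments section gives three outcomes the same rank: "The primary outcome measures are aerobic fitness, energy expenditure and physical activity". The abstract does likewise: "Primary outcomes are aerobic fitness, 12-hour energy expenditure, and proxy-reported everyday physical activity". The Discussion again lists all three as primary and counts the proxy questionnaire (IPAQ-ID) among them.

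The Analyses section assigns repeated-measures ANOVA to all primary and secondary outcomes at 3 and 9 months, and then states "Significance will be set to *p* < 0.05". It does not rank the primary outcomes, divide alpha among them, or say whether one, two or all three must be positive.

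On power, the Sample size section says "We will power the study based on the primary outcome of aerobic fitness". It sets alpha 0.05, power 0.95, f = 0.40, three groups, three repeated measures and a correlation of 0.5. This requires 69 evaluable participants, and "we will recruit 30 participants per group for a total sample of 90" to allow for attrition.

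The Background sets the comparisons of interest. Both approaches are to be "evaluated and compared to a usual-care control group", and they are also compared with each other at 3 and 9 months: "By contrasting two different approaches to increased physical activity we will compare the short-term (3-month) and long-term (9-month) effectiveness and sustainability of both strategies".

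**The concern.** With three primary outcomes and one unadjusted threshold, the trial has three chances to produce a positive primary result. The 5% level then describes each outcome separately and not the risk of a false primary claim from the trial.

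This matters here because the outcomes differ in robustness. Participants and assessors are un-blinded, and the IPAQ-ID is reported by carers. With no order stated, nothing in the article prevents p < 0.05 on that measure alone from being reported as a positive primary outcome while VO2peak, the only powered outcome, shows no effect. The Discussion links a successful result to wider use of the approach by disability services.

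**Working it through.** **1. The plan's own sample size.** Inputs from the Sample size section: f = 0.40, k = 3 groups, m = 3 measures, ρ = 0.5, alpha 0.05, power 0.95. For the between-groups test in repeated-measures ANOVA:

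λ = f² × N × m / (1 + (m − 1)ρ), with df = k − 1 and N − k.

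- N = 69: λ = 0.16 × 69 × 3 / 2 = 16.56, df 2 and 66, power 0.955.
- N = 66: λ = 0.16 × 66 × 3 / 2 = 15.84, power 0.945.

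The smallest N in multiples of three is therefore 69, as stated. Attrition is 1 − 69/90 = 23.3%, which also agrees. The group-by-time test with the same inputs would need only 24. So 69 belongs to one between-groups omnibus test, of one outcome, at an unadjusted 0.05.

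**2. One omnibus test per primary outcome (the most lenient reading).** If the three tests are independent:

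1 − 0.95³ = 0.143.

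The article gives no correlation between the outcomes, so it was varied in a simulation in which neither intervention has any effect (10,000 trials per setting, 23 per group, within-person correlation 0.5). The columns show the chance of at least one p < 0.05.

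| Assumed outcome correlation | 3 between-group tests | 3 group-by-time tests |
|---|---|---|
| 0 | 14.0% | 14.3% |
| 0.3 | 13.0% | 13.3% |
| 0.5 | 12.6% | 12.8% |
| 0.8 | 9.9% | 10.3% |

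**3. Readings that add arms and visits** (same simulation, outcome correlation 0.8 to 0):

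- Pairwise contrasts only after a significant group-by-time F test at 0.05: 10–13%. A gate within each outcome does not deal with having three outcomes.
- One omnibus test per outcome at each follow-up visit (6 tests): 18–25%.
- Every arm pair at each follow-up visit with no gate (3 outcomes × 3 pairs × 2 visits = 18 tests): 38–51%. A separate simulation of baseline-adjusted tests (6,000 runs, outcome correlation 0.5 to 0) gave 47–52%. Treating the 18 tests as independent would give 1 − 0.95¹⁸ = 60.3%, which is too high because the contrasts share arms and participants.

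**4. Cost of adjustment.** Bonferroni over three outcomes uses 0.05/3 = 0.0167 for each. In the formula of step 1, omnibus power becomes 89.1% at N = 69 and 96.5% at N = 90. Restoring 95% would take 84 evaluable, or 84/0.77 = 109.1, so 110 recruited. A fixed order tests VO2peak first at the full 0.05 and leaves 69 and 95% unchanged for it.

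**The case against.** **A reader might infer that 18 pairwise tests are planned at 0.05 and that the false positive risk is about one half.** The article does not support this. It names repeated-measures ANOVA, in which arm and visit are factors in one model per outcome, and the stated 69 reproduces as a single omnibus test. The Background does list comparisons with control, between interventions and at two visits, but nowhere says that each is an ungated test at 0.05. The 38–52% is therefore a conditional upper scenario.

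**A reader might also infer that the sample size already makes VO2peak at 3 months the single primary endpoint.** It does not. The calculation uses three repeated measures and names no visit, and powering on an outcome does not make it a gatekeeper for the others.

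**The article is condensed and an analysis plan may exist.** Post-hoc procedures and contrast adjustments are commonly left to such a plan, and a p-value threshold of 0.05 could be applied to adjusted p-values. This answers the arm and visit layer, where the article is merely silent. It does not answer the three-outcome layer: the article itself fixes three unranked primary outcomes and a flat threshold, and calculates power at an unadjusted 0.05. ANOVA pools arms and visits within an outcome but cannot combine outcomes.

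**Demoting two primary outcomes, or the 9-month results, would cut against the stated aims.** This stands. Long-term sustainability ranks level with short-term effect in the Background, and the Discussion deliberately treats the IPAQ-ID as primary. The remedy should therefore keep all of them.

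**Conclusion.** The point holds for the three primary outcomes. Followed as written, the plan carries about a 10–14% chance of at least one false positive primary finding when neither intervention works, two to three times the nominal 5%. The range rests on one omnibus test per outcome and on outcome correlations assumed between 0.8 and 0. Arms and visits would raise the risk only if their contrasts were tested without a gate, which the article leaves open. The sample size arithmetic is correct, but it supports one outcome tested once at 0.05.

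**What to change.** In the Analyses section, hold the error across the three primary outcomes at 5% by one of two routes:

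- **Holm across the three omnibus tests.** All three outcomes keep equal standing. The price is the Bonferroni first step: omnibus power for VO2peak falls from 95% to about 89% at 69 evaluable, or is 96.5% if all 90 are evaluable. The Sample size section should restate this.
- **A fixed order starting with VO2peak.** Each outcome is tested at 0.05 only if the one before it succeeded. Power for VO2peak stays at 95% with 69 evaluable, but no confirmatory claim on the other two outcomes is possible if VO2peak fails.

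Under either route, say which F test is the omnibus test, and test the arm contrasts for an outcome only after that test is significant at its allotted level. The power figures above belong to the between-groups test and would change with another choice. Keep all three outcomes and the 9-month assessment in the plan. The change takes a few sentences and needs no extra participants unless the sponsor wants 95% power under Holm.

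### Intention to treat is promised, but the only between-group method named, repeated-measures ANOVA, in its standard form drops any participant with a missed visit

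*Protocol article*

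**What the plan says.** The Analyses section of the protocol article names one method for between-group comparison: "Repeated-measures ANOVA will be used to compare both the intervention and control group participants on primary and secondary outcome measures". It is meant for both follow-up visits. Multiple regression is mentioned only for identifying characteristics associated with better outcomes. The same paragraph then fixes the analysis population: "Analysis will be on the basis of intention to treat, with a secondary per-protocol analysis".

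The Outcome assessments section sets three visits: "All outcomes will be assessed at baseline, 3-months post-baseline and at 9-months post-baseline".

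The Sample size section powers the trial for the same ANOVA and finds that "this would require a total sample size of 69 (i.e., 23 per group), to analyse between-group differences using repeated measures ANOVA". It then plans a margin: "we will recruit 30 participants per group for a total sample of 90, which allows for 23% attrition without compromising power".

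The article mentions no imputation, mixed model or other means of keeping a participant with a missed visit in the comparison.

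**The concern.** Standard repeated-measures ANOVA works on complete rows. A participant with valid baseline and 3-month VO2peak who misses month 9 is removed altogether, so the 3-month comparison loses a value that was collected. Run as written, the named method would analyse those who attended every visit, which is not everyone as randomised. The article fixes both the method and the population, and the two do not fit together once visits are missed.

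Two things are at stake. One is efficiency, because observed 3-month data are discarded. The other is possible bias, because participants who complete all visits are no longer a randomised comparison if the reasons for leaving are related to outcome and differ by arm. The arms do place different demands on participants: three group classes a week, a weekly specialist session plus staff-supported activity, or usual activities. After week 12 delivery passes to disability staff alone for six months. Outcome-related dropout that differs by arm is therefore possible, though the article gives no figures on it.

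**Working it through.** **Step 1. Reproduce the plan's sample size.** Inputs from the Sample size section: f = 0.40, k = 3 groups, m = 3 measures, correlation ρ = 0.5, α = 0.05, power 0.95. For the between-groups effect in repeated-measures ANOVA:

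λ = N·f²·m / (1 + (m − 1)ρ), with k − 1 and N − k degrees of freedom.

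- N = 69: λ = 69 × 0.16 × 3 / (1 + 2 × 0.5) = 16.56, power 0.955.
- N = 66: λ = 15.84, power 0.945.

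The smallest multiple of 3 that reaches 0.95 is 69, as stated. The test that was powered is the group effect averaged over visits; the group-by-time version of the formula would need only 24.

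**Step 2. Reproduce the attrition margin.** 90 − 69 = 21, and 21/90 = 23.3%, as stated. Per arm, 30 − 23 = 7. The arithmetic is right.

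**Step 3. What the named method does at that margin.** If 21 participants each miss at least one visit and nothing is imputed, the ANOVA uses 69 of 90. Power is then 0.955. With complete data on all 90 (λ = 21.6) it would be 0.988. A method that keeps partial data would fall between the two. Power is not the problem; who is analysed is.

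**Step 4. Size of a possible bias (illustration).** These assumptions are not in the article, except that ρ = 0.5 is taken from its sample-size inputs:

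- unit SD at each visit, normal data, true group difference zero;
- exercise-arm dropout more likely with a low 3-month value, logistic slope 1 per SD;
- control dropout random. Its rate then does not affect the bias, so a 23%/23% split and a 31%/15% split differ only through the exercise arm.

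The mean shift among exercise-arm completers at 3 months is 0.197 SD at 23% dropout and 0.261 SD at 31%. With ρ = 0.5, the shift at baseline and at 9 months is half of that.

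| Exercise-arm dropout | Baseline | 3 months | 9 months |
|---|---|---|---|
| 23% | 0.099 | 0.197 | 0.099 |
| 31% | 0.130 | 0.261 | 0.130 |

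From these shifts, the bias in what the ANOVA tests is:

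- Change from baseline at 3 months: 0.197 − 0.099 ≈ 0.10 SD; 0.261 − 0.130 = 0.13 SD.
- Change from baseline at 9 months: 0.099 − 0.099 = 0; 0.130 − 0.130 = 0.
- Average over the three visits: (0.099 + 0.197 + 0.099)/3 = 0.13 SD; (0.130 + 0.261 + 0.130)/3 = 0.17 SD.

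Against the assumed d = 0.80, this is about 12% to 16% for the 3-month change and about 17% to 22% for the average over visits.

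**Step 5. Sensitivity to the slope.** At slope 0.5 the 3-month change bias is 0.06 SD (23% dropout) to 0.07 SD (31%). At slope 0 every bias is nil.

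**Step 6. Does the alternative help?** In a simulation at 23% dropout with slopes 0 to 1.5, a likelihood-type estimate of the 9-month difference that used the earlier visits stayed within 0.005 SD of the truth, for true differences of 0 and 0.8. The raw completer 9-month difference was too favourable by about 0.05 to 0.13 SD at slopes 0.5 to 1.5.

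**The case against.** The strongest reply is that the article nowhere says missing visits will be deleted. ANOVA after imputation is compatible with intention to treat, and a condensed article may leave missing-data handling to a fuller document. This stands in part: it cannot be said that the main analysis will certainly be restricted to completers. It does not remove the point. The article does choose a method, and in its standard form that method fails to deliver the population promised in the same paragraph. Naming a better-suited method is a concrete change to something the article has fixed.

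Three stronger readings are tempting, and the document does not support them.

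- A reader might infer from "which allows for 23% attrition without compromising power" that only 69 participants are meant to be analysed. That sentence inflates recruitment, which is routine under any analysis model. It is an allowance. It does not forecast dropout or define an analysis set.
- A reader might take the raw 3-month completer difference of 0.20 to 0.26 SD, or 25% to 33% of d = 0.80, as the bias. That ignores baseline, which is one of the three repeated measures. The bias in what the named ANOVA tests is smaller (Step 4).
- A reader might infer that dropout will favour the exercise arm. The article gives no attrition by arm. Unequal rates alone do not bias a completers comparison, and poor performers leaving the control arm would reverse the direction.

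**Conclusion.** The point holds as an inconsistency between the named method and the promised population, and it should be fixed. At the planned attrition margin, up to 21 of 90 randomised participants (23.3%), including any observed 3-month values, would fall outside the analysis unless values are imputed first. The stated sample size and attrition arithmetic are correct.

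If dropout is unrelated to outcome, the consequence is lost data only. The bias figures of 0.10 to 0.13 SD (3-month change), about 0 (9-month change) and 0.13 to 0.17 SD (average over visits) rest on an assumed dropout mechanism, slope and exercise-arm rate. They show a plausible order of size and do not predict what will happen. They do not justify calling the main analysis invalid.

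**What to change.** In the Analyses section, replace repeated-measures ANOVA with a likelihood-based linear mixed model for repeated measures. State that it includes every randomised participant as allocated, with all available visits and no listwise deletion. Multiple imputation before the ANOVA is an acceptable alternative if the authors wish to keep the named method; the text should then say so. Keep the completers analysis as a sensitivity analysis.

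The cost is a change of wording and slightly more analysis work, with no new data and no larger sample. The main analysis would then rely on a missing-at-random assumption, which should be stated.
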